# Oral salt and water versus intravenous saline for the prevention of acute kidney injury following contrast-enhanced computed tomography: study protocol for a pilot randomized trial

**DOI:** 10.1186/s40697-015-0048-7

**Published:** 2015-04-16

**Keywords:** **C**ontrast-induced nephropathy, Oral Salt and Water, Intravenous saline, Randomized controlled trial

## Abstract

**Background:**

Although intravenous saline is the accepted prophylactic measure for the prevention of contrast- induced acute kidney injury, the oral route could offer an equivalent, practical, and cost saving approach. A systematic review of randomized trials that compared oral versus intravenous volume expansion for the prevention of radiocontrast-induced nephropathy in patients receiving arterial contrast reported no significant difference in the risk of contrast induced acute kidney injury between the oral and intravenous arms. Most trials for contrast nephropathy prevention have been in the setting of arterial contrast such as with cardiac catheterization, and not with venous contrast, such as computed tomography. The aim of this paper is to describe the protocol of a pilot trial comparing the effect of oral salt and water versus intravenous saline on the prevention of Acute Kidney Injury following contrast-enhanced computed tomography.

**Methods:**

Our study is a pilot, single-centre parallel randomized controlled trial. To be included, participants must be at stage 4 of chronic kidney disease as defined by a glomerular filtration rate <30 mL/min/1.73 m^2^, aged greater than 18 years and to undergo an outpatient contrast-enhanced computer tomography of the chest or abdomen. A total 50 patients will be randomised to receive either oral salt and water or intravenous isotonic saline. The primary outcome is feasibility, including estimates of recruitment rate, adherence to intervention and completeness of follow-up to assist in planning the definitive trial. The secondary outcome is safety and includes adverse events with oral salt and water loading as compared to intravenous isotonic saline.

**Discussion:**

The results of this pilot trial will provide critical information to plan a definitive trial to test the efficacy of the route of volume loading regimens in prevention of acute kidney injury after contrast-enhanced CT scans.

**Trial registration:**

The trial is registered at the US National Institutes of Health (ClinicalTrials.gov) # NCT02084771.

## Background

Since its invention, computed tomography (CT) has greatly improved diagnostics and patient care. Over 50% CT procedures employ iodinated contrast material (CM) [1]. At the same time as the CT scan use has rapidly increased [2], it has been estimated that more than 80 million doses of CM are administrated worldwide each year [3]. Thus, since the number of CT scan examinations increase, their adverse effects, including renal failure, also potentially increase.

Acute kidney injury is a common form of nephropathy induced by contrast medium reported by several studies [4-10]. Contrast-induced acute kidney injury (CI-AKI) is associated with long- term adverse outcomes including stroke, myocardial infarction, long term dialysis dependence, and death [11-15]. The average in-hospital cost of CI-AKI is estimated at $10,345 with the 1- year cost of treating a patient with CI-AKI at $11,812 [16]. Thus, there is considerable interest in developing strategies aimed at reducing the risk of CI-AKI.

Hydration is clearly beneficial in prevention of CI-AKI [17]. The Canadian guideline for chronic kidney disease patients who have contrast-enhanced computed tomography scans is to give intravenous (IV) saline both before and after their CT scan. Recommended protocols require that saline be given in the one hour before and in the six hours following contrast administration and have been formulated for arterial contrast (e. g. cardiac or peripheral angiography), where patients do need a short stay for monitoring [18,19]. For contrast CT, this requires additional nursing time and resources to monitor patients during the infusion (approximately 7–8 hours per patient). This regimen requires significant health care resources as it requires a same-day hospital stay, nursing time as well as patient inconvenience.

Oral salt and water solutions are well tolerated and effective in prevention and treatment of dehydration [20-23]. Mechanistic studies have also established that oral sodium and water loading results in rapid (within 20 minutes) changes in physiology with a significant increase in cardiac output and subsequent diuresis [24-26]. We performed a systematic review of randomized trials that compared oral versus intravenous volume expansion for the prevention of radiocontrast-induced AKI [27]. Our search identified six small studies (average sample size n = 85), all done in patients receiving arterial contrast [28-33]. We pooled all six trials together in a meta-analysis and found no significant difference in the odds of AKI between the oral and intravenous fluid arms (summary odds ratio 1.2; 95% CI 0.46 to 3.10; P = 0.73). Taken together, these data show that there is no clear trial evidence favouring intravenous over oral fluid expansion. Moreover, mechanistic evidence suggests that a sufficient proportion of an acute oral salt and water load is absorbed to have measurable physiological effects within 30 minutes [24,34].

However, most of the trials for contrast nephropathy prevention have been in the setting of arterial contrast such as with cardiac catheterization, and not with venous contrast, such as computed tomography. The advantages of an oral route of volume expansion in this setting would include decreased use of hospital resources and cost, reduced time in hospital as well as improved patient comfort and convenience [33,35,36]. The 2012 guidelines from the Kidney Disease: Improving Global Outcomes (KDIGO) workgroup state that, “if confirmed in larger studies, the oral strategy could offer an equivalent and more practical approach in preventing a decline in renal function after contrast exposure, without accruing additional delay in hospital days or in-hospital mortality” [37]. In addition, the trials we identified in our systematic review were all small, none was powered to study important clinical outcomes.

We are conducting a pilot randomized trial with the objective to measure the feasibility of a trial (recruitment, adherence to intervention, completeness of follow up) and the safety outcomes (adverse effects with the intervention). This will provide crucial information required to facilitate the planning of an adequately powered, definitive, randomized controlled trial comparing the effect of oral salt and water administration versus intravenous saline in the prevention of CI-AKI occurring after an intravenous (IV) contrast administration. This protocol describes the design and methodology of the pilot randomized trial.

## Methods

### Design and setting

The study is designed as a single-centre, parallel-arm, randomized controlled pilot trial. Participants will be recruited from the Ottawa Hospital, an academic centre serving a catchment area of 1.3 million residents in Eastern Ontario (Ottawa and environs), Canada.

### Participants

Participants will be identified within the medical imaging department. Eligible patients are outpatients who are scheduled for a contrast-enhanced CT scan of the chest or abdomen. We plan to enrol 50 patients in this pilot trial. Since this is a pilot trial to assess feasibility, we did not carry out a formal sample size calculation. The rate of recruitment in this trial will allow us to plan the recruitment strategy and duration of the definitive trial. For the large definitive trial (planned as a non-inferiority trial) our preliminary estimates for sample size suggests we need to recruit 1030 patients.

### Criteria

#### Inclusion criteria

Chronic kidney disease (as defined by a glomerular filtration rate (GFR) < 30 mL/min/1.73 m^2^ using the Chronic Kidney Diseases (CKD)-EPI formula calculated on the day of screening [38];Undergoing an outpatient intravenous contrast-enhanced CT of the chest or abdomen;Age ≥ 18 years

### Exclusion criteria

Inability to give informed consent;Previously enrolled in this study;Any contrast-enhanced test in previous 14 days (to exclude patients who might have ongoing AKI from previous contrast exposure);Congestive heart failure defined as NYHA class III or worse [39];Uncontrolled hypertension defined as SBP greater than 180 mm Hg or DBP greater than 110 mm Hg at screening;Currently receiving dialysis treatments.The physician ordering the CT scan has specifically ordered intravenous saline, sodium bicarbonate or n-acetyl cysteine.Scheduled to receive oral contrast solution as part of CT scan procedure

### Patient identification and recruitment

A chart review will be performed on all patients with scheduled contrast-CT scans of the chest or abdomen by department personnel. Potential participants will be approached by phone calls as per local study-specific Research Ethical Board -approved procedures and Standard Operating

Procedures. Potential participants who consent will be invited for a screening visit where they will be asked to give a blood sample to analyze their serum creatinine (SCr) levels. This will serve to calculate the estimated GFR used in the screening process. Final inclusion/exclusion criteria will be assessed and confirmed by the Principal Investigator and Co-Investigator only. Consenting patients fulfilling entry criteria will be successively recruited. The Consolidated Standards of Reporting Trials flow diagram will be used to show the study flow chart (Figure 1.)

**Figure 1 Fig1:**
[figure not shown]
**Study flow chart.**

### Randomization and allocation concealment

Patients will be randomized to receive either oral salt and water or intravenous saline. The randomization process will consist of a computer generated random listing of the treatment allocations in permuted blocks of varying size. For example, given a block size of 4 patients recruited, there will be 2 allocations to oral salt and water arm and 2 to the intravenous saline arm. The system will have backup in the form of an independent statistician who will be informed and able to issue the treatment allocation in the event of a system malfunction/shutdown.

The randomization will be performed independently by a statistician after eligibility is documented by the Principal Investigator/Co-Investigators based on inclusion/exclusion criteria and after the patient signs the informed consent. From the computer random listing a code will be assigned to each new subject. This randomization code is a participant unique identifier (ID) and corresponds to the study treatment that will be given to the patient. Patient will be considered randomized as soon as the randomization code is given. All patients who are allocated a randomization code (i.e., study treatment number) will be irrevocably in the study and they will be followed until the end of study, loss to follow-up or death whichever comes first. The randomization codes corresponding to the participant ID will be printed and put in numbered sealed envelopes. On the day of the CT scan, these envelopes will be delivered to the imaging room to be opened by the Principal Investigator who will administer the trial treatment.

### Blinding

Blinding of the intervention is extremely difficult as one intervention will be oral and the other intravenous. A double-dummy design could be considered but the “dummy” intravenous fluid would likely have some volume expanding effect that could affect the outcome. Aside from the ethical consideration, a sham infusion could be considered but may prove difficult with back flow of blood from the venous cannula if no infusion were occurring. To minimize co- interventions that might be given once treatment assignments are known, participants, radiology staff and the ordering physician will not be informed of the treatment assignment prior to the scheduled CT, which will minimize the chance of the treating team providing additional therapies based on knowledge of the treatment assignment. All trial interventions will be administered by the Principal Investigator out of sight of imaging staff.

### Trial intervention and dosing

#### The oral salt and water arm

Participants randomized to this arm of the trial will receive 0.1 g/kg of salt (NaCl) in capsule form and 12 mL/kg of water. Patients weighing more than 110 kg will receive the same amount as per a 110 kg patient [18]. This dosage was based on the trial of Dussol et al. in which oral salt was given using a pre-specified, weight-based approach [32]. This trial showed that 50% more oral salt ingestion, compared to intravenous saline, produced equivalent urinary sodium excretion. We have used these proportions to formulate the equivalent oral salt dosing. The oral water dosing has been calculated to make the overall composition approximately isotonic similar to the intravenous saline arm. One third of the oral salt and water will be given in 1 hour before the CT and 2/3 in the 2 hours post-CT. Specifically, 0.03 g/kg of NaCl and 4 mL/kg of water in the one hour before CT and 0.07 g/kg of NaCl and 8 mL/kg of water taken over 2 hours post-CT. The salt capsule and water will be taken in presence of the research personnel who will record on an assessment form that the patient has received the intervention (ingested the oral salt and water).

### The intravenous saline arm

Patients randomized to this arm will receive IV isotonic (0.9%) saline which is the standard of care recommended by Canadian [19] and international guidelines [8,40-44]. The rate of isotonic saline will be 3 mL/kg given in the one hour before CT and 1 mL/kg/hour for 6 hours post-CT as per Canadian guidelines [19]. Patients weighing more than 110 kg will receive the rate as per a 110 kg patient [18]. The dose will be rounded up to the nearest 5 mL.

### Data collection

At baseline, participant demographic information (including ethnicity, sex, month and year of birth), CT scan characteristics, medical history and medication use will be recorded. On the day of the CT scan, before oral or IV fluids are given, a SCr will be measured that will be considered as the baseline value. A subsequent SCr level will be measured at 48 hours post-CT. If the SCr at 48 hours has increased by ≥25% or ≥44 μmol above the baseline value, the SCr will be repeated every 48 hours until it returns to within 25% of baseline or < 44 μmol above baseline or the patient needs to initiate acute dialysis. If the SCr has not returned to within 25% of baseline or < 44 μmol above baseline by day 14 post-CT, the SCr will be measured again on day 21. All participants (regardless of whether they developed AKI) will have SCr repeated on day 28 post- CT (Figure 2). The SCr will be measured in the biochemistry lab at the Ottawa Hospital. The repeat creatinine measurements, though underpowered for any assessment of efficacy, will allow us to ascertain the proportion of patients who follow-up at each time point, which will be critical for our larger definitive trial. The study timeline is shown in Table 1.

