### Outcomes

Feasibility of conducting the definitive trial is the primary outcome for this pilot study. It will be determined by the proportion of patients who will 1) consent to enrolment in the study (recruitment rate), 2) complete the fluid ingestion at dose required in both arms (adherence to intervention), and 3) complete repeat measures of creatinine at 48 hours and 28 days (follow-up). Additionally, we will identify logistical issues related to screening, protocol implementation, randomization implementation strategy, time, and budget problems that can occur during the definitive trial.

The secondary outcome for this pilot trial is safety. It will be assessed by adverse effects occurring after receiving the trial treatment. Adverse effects that may occur because of the ingestion of water and salt include: nausea or gastrointestinal symptoms. Symptoms that may occur because of the saline solution or the technique of administration include discomfort with the venipuncture at the site of injection such as skin irritation and pain, hemorrhage, hematoma, thrombosis, phlebitis. All adverse events effects will be assessed by patients self-reported symptoms using a questionnaire with these symptoms listed and will be recorded in a Case Report Form at the end of the volume expansion protocol.

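### The stop condition for repeat creatinine testing is not the complement of the start condition, so some values literally both start and stop retesting

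*Protocol article*

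**What the plan says.** All the relevant rules are in the Data collection section of the protocol article.

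- **Baseline.** On the day of the CT, "before oral or IV fluids are given, a SCr will be measured that will be considered as the baseline value".
- **Start.** Retesting is triggered as follows: "If the SCr at 48 hours has increased by ≥25% or ≥44 μmol above the baseline value".
- **Stop.** Once triggered, "the SCr will be repeated every 48 hours until it returns to within 25% of baseline or < 44" μmol above baseline, or until acute dialysis is needed.
- **Day 21.** An extra test on Day 21 is due under this condition: "If the SCr has not returned to within 25% of baseline or < 44 μmol above baseline by day 14 post-CT".
- **Day 28.** "All participants (regardless of whether they developed AKI) will have SCr repeated on day 28 post- CT".

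The same section says that the repeat measurements are underpowered for efficacy. It says they will show what proportion of patients attend at each time point, and it calls this critical for the definitive trial. In the Outcomes section, the follow-up part of the primary feasibility outcome counts only the 48-hour and 28-day creatinine values. Table 1 marks post-allocation creatinine at Day 3 and Day 28 and shows no triggered repeats. Figure 2, titled as the repeat creatinine test schedule, is not visible in the text available for this review.

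**The concern.** A rule that starts on one condition and runs until that condition has cleared needs a stop condition that is true exactly when the start condition is false. If either of two criteria starts retesting, the logical opposite is that neither is met. The article instead joins the two recovery criteria with 'or', so recovery on one is enough even when the other is still met.

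Two things are at stake. The first is monitoring. A patient flagged with a creatinine rise after contrast could, on the literal wording, have no further test required by the visible text until Day 28. The second is the feasibility information. If staff can read the rule in different ways, it is unclear who is due a test at each triggered time point, and so the denominator for attendance there is unclear too. The definitive trial is to have AKI incidence as its primary outcome, so the wording could be carried into a setting where it matters more.

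**Working it through.** The document gives no figure of its own to reproduce for this rule. The check is one of logic, followed by a size estimate on stated assumptions. The article writes the absolute threshold in μmol; I read it as μmol/L.

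**Step 1: truth table.** Let A = rise of at least 25% and B = rise of at least 44 μmol/L.

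- Start, as written: A or B.
- Stop, as written: not-A or not-B.
- Logical complement of start: not-A and not-B.

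| A | B | Start | Stop as written | Complement of start |
|---|---|---|---|---|
| no | no | no | yes | yes |
| no | yes | yes | **yes** | no |
| yes | no | yes | **yes** | no |
| yes | yes | yes | no | no |

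In two of the three triggering rows, start and stop are both true. A patient in the last row moves to one of the two middle rows as soon as one criterion resolves. That patient then meets the stop condition while still meeting a trigger. The Day 21 sentence requires a test only if the written stop condition has not been reached by Day 14, so a patient with exactly one criterion still met at Day 14 gets none.

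**Step 2: which values are affected.** The thresholds coincide where 0.25 × baseline = 44, that is at a baseline of 44/0.25 = 176 μmol/L. Elsewhere the rises that meet exactly one trigger run from the smaller of (0.25 × baseline, 44) up to, but not including, the larger. The article gives no creatinine distribution, so the baselines below are assumptions.

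| Baseline (μmol/L) | 25% of baseline | Rises meeting exactly one trigger |
|---|---|---|
| 120 | 30 | 30 to <44 |
| 150 | 37.5 | 37.5 to <44 |
| 176 | 44 | none |
| 200 | 50 | 44 to <50 |
| 250 | 62.5 | 44 to <62.5 |
| 300 | 75 | 44 to <75 |
| 400 | 100 | 44 to <100 |

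At a baseline of 250, a rise of 50 is 50/250 = 20%. It starts retesting on the absolute criterion and is already within 25%. A rise of 70 is 28%; it meets both triggers and does not meet the stop condition.

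**Step 3: how many patients.** Assumptions: GFR uniform on 15 to 30, age uniform on 55 to 85, equal sexes, baseline creatinine from the inverted CKD-EPI equation, and log creatinine change normal with mean 0 and the SD shown. Under these, 83% of baselines exceed 176 μmol/L.

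| SD of log change | Participants triggered | Of those triggered, stop already met | Share of all participants | Out of 50 |
|---|---|---|---|---|
| 0.10 | 4.0% | 70% | 2.8% | 50 × 0.028 = 1.4 |
| 0.15 | 11.6% | 43% | 4.9% | 50 × 0.049 = 2.5 |
| 0.20 | 18.2% | 29% | 5.3% | 50 × 0.053 = 2.7 |
| 0.30 | 27.2% | 17% | 4.6% | 50 × 0.046 = 2.3 |

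The share of triggered patients is largest when few patients trigger at all, so the count out of 50 is the better guide to size. With GFR uniform on 20 to 30 instead, the count falls to about 0.8 to 1.8 of 50. These figures concern the 48-hour measurement only. They do not count patients who meet both triggers first and are released later.

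**The case against.** The best defence is that the literal reading is not the natural one. A value that is to be repeated until it returns has first to have left the range, so it can hardly return at the same measurement that triggered the repeat. The sentence might mean at least one repeat. It might also pair each recovery criterion with its own trigger: a 25% rise followed until within 25%, and a 44 μmol rise followed until below 44. Figure 2 may settle this, and the full protocol behind the article may be clearer.

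Part of this stands. The text is ambiguous, so it is not certain that tests would be omitted. Requiring one repeat removes the immediate stop at 48 hours. It does not remove the release of a patient who still meets one trigger, or the Day 21 gap. The paired reading would cure all three, but nothing in the visible text states it.

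The effect on the pilot's outcomes is also small, and this stands. The primary follow-up outcome uses two fixed time points, 48 hours and Day 28. The safety outcome is a symptom questionnaire completed at the end of volume expansion. Serious adverse events go to the DSMB, and the section schedules study measurements without limiting clinical care.

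A reader might infer that a single-trigger patient has no AKI follow-up at all. The documents do not support that, because every participant has a Day 28 creatinine. A reader might also infer from the 70% figure that the problem is common in the trial. That figure is a share of triggered patients in the scenario where only 4.0% trigger, and it corresponds to about 1.4 participants of 50.

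**Conclusion.** The point holds as a fault in the written rule. The start and stop conditions overlap, and the Day 21 sentence repeats the overlap. The supported consequence is that patients meeting one trigger, or still meeting one after the other has resolved, could lose the intermediate repeats and the Day 21 test. It also leaves unclear who is due a test at the triggered time points.

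The logic rests on the text alone. The size, about 1.4 to 2.7 of 50 participants at 48 hours, rests on assumed GFR, age, sex and creatinine-change distributions that the article does not give. The primary follow-up estimate does not change. I rate this moderate: worth correcting for consistent monitoring and for carry-over to the definitive trial, but no threat to the pilot's main results. Figure 2 could show that the intended rule is already clear to staff, in which case only the text needs correcting.

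**What to change.** Reconcile the start, stop and Day 21 conditions so that no creatinine value can both start and stop retesting, and so that the Day 21 condition uses the same definition of recovery as the stop condition. If the investigators mean each recovery criterion to go with its own trigger, or a minimum number of repeats, the text should say so. Then check that Figure 2 shows the same rule. Which thresholds apply, and which clinical rule is intended, are for the investigators to decide.

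The cost is a change of wording in two sentences and a check of one figure. Depending on the rule intended, a few triggered patients may have more blood draws than the literal text requires. No analysis or sample size changes.
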